## Abstract

**Background:**

People with COVID-19 are instructed to self-isolate at home. During self-isolation, they may experience anxiety and insufficient care. Patient portals can allow patients to self-monitor and remotely share their health status with health care professionals, but little data are available on their feasibility.

**Objective:**

This paper presents the protocol of the Opal-COVID Study. Its objectives are to assess the implementation of the Opal patient portal for distance monitoring of self-isolating patients with COVID-19, identify influences on the intervention’s implementation, and describe service and patient outcomes of this intervention.

**Methods:**

This mixed methods pilot study aims to recruit 50 patient participants with COVID-19 tested at the McGill University Health Centre (Montreal, Canada) for 14 days of follow-up. With access to an existing patient portal through a smartphone app, patients will complete a daily self-assessment of symptoms, vital signs, and mental health monitored by a nurse, and receive teleconsultations as needed. Study questionnaires will be administered to collect data on sociodemographic characteristics, medical background, implementation outcomes (acceptability, usability, and respondent burden), and patient satisfaction. Coordinator logbook entries will inform on feasibility outcomes, namely, on recruitment, retention, and fidelity, as well as on the frequency and nature of contacts with health care professionals. The statistical analyses for objectives 1 (*implementation outcomes*), 3 (*service outcomes*), and 4 (*patient outcomes*) will evaluate the effects of time and sociodemographic characteristics on the outcomes. For objectives 1 (*implementation outcomes*) and 4 (*patient outcome*s), the statistical analyses will also examine the attainment of predefined success thresholds. As for the qualitative analyses, for objective 2 (*influences on implementation*), semistructured qualitative interviews will be conducted with 4 groups of stakeholders (ie, patient participants, health care professionals, technology developers, and study administrators) and submitted for content analysis, guided by the Consolidated Framework for Implementation Research to help identify barriers to and facilitators of implementation. For objective 3 (*service outcomes*), reasons for contacting health care professionals through Opal will also be submitted for content analysis.

**Results:**

Between December 2020 and March 2021, a total of 51 patient participants were recruited. Qualitative interviews were conducted with 39 stakeholders from April to September 2021. Delays were experienced owing to measures taken at the McGill University Health Centre to address COVID-19. The quantitative and qualitative analyses began in May 2022. As of June 2022, a total of 2 manuscripts (on the implementation and the patient outcomes) were being prepared, and 3 conference presentations had been given on the study’s methods.

**Conclusions:**

This protocol is designed to generate multidisciplinary knowledge on the implementation of a patient portal–based COVID-19 care intervention and will lead to a comprehensive understanding of feasibility, stakeholder experience, and influences on implementation that may prove useful for scaling up similar interventions.

**Trial Registration:**

ClinicalTrials.gov NCT04978233; https://clinicaltrials.gov/ct2/show/NCT04978233

**International Registered Report Identifier (IRRID):**

DERR1-10.2196/35760

## Introduction

### Background

As of December 13, 2021, over 267 million people worldwide have had COVID-19, including almost 2 million in Canada [1]. In 2020, without effective vaccines or treatments, governments and public health agencies enforced lockdown and distancing measures to limit the spread of COVID-19 and the burden on health care systems. At the time, in the Canadian province of Québec, 95% of people diagnosed with COVID-19 were instructed to self-isolate at home and contact health care services if their health deteriorated. While most patients with COVID-19 have mild to no symptoms in the first week following infection [2,3], patient health can rapidly deteriorate in the second week and opportunistic infections can appear [4]. Quick recognition of worsening health is crucial to avoid delays in health care and improve prognosis. However, most self-isolating patients lack tools to self-monitor their illness and maintain contact with health care professionals to ensure timely care. Self-isolation for COVID-19 can also cause anxiety, especially among vulnerable, older, or low-literacy patients [5,6], owing, in part, to inadequate information [7]. Furthermore, it can contribute to numerous other problems, including substance use or addictions [8], self-harm [9], and interpersonal difficulties [10]. Interventions to help self-isolating patients monitor symptoms and vital signs, provide them with educational materials, and facilitate communication with health care professionals could increase the safety and timeliness of care, while reducing psychological distress [5-7].

Health information technologies (HITs) offer solutions in this regard, and the pandemic has propelled their use, including in the form of telehealth and education platforms [11]. Among HITs, patient portals can provide important information and facilitate interactions between self-isolating patients and health care professionals. Their use is also associated with improved patient engagement, empowerment, and satisfaction [12]. One such portal, Opal, was initially created for use at the Cedars Cancer Centre at the McGill University Health Centre (MUHC) in Montreal, Canada, where our team is based. Implemented in 2018, it was co-designed by health care professionals, patients, and HIT developers [12]. It includes a patient smartphone app and a physician desktop dashboard. With Opal, among other advantages, oncology patients can view their diagnostics and treatment plan, laboratory test results, appointment and test schedules, clinical consultation notes, and tailored educational material. Using a dashboard designed for them, health care professionals can administer patient-reported health measures and communicate with patients between consultations [13].

To support self-isolating patients with COVID-19, our team decided to configure Opal for this purpose. This involved applying an existing HIT to a novel and different context of use. Although the benefits of HITs are well-documented for the follow-up of chronic conditions [14-16] such as cancer, little is known about their transferability to acute and typically short-term conditions such as COVID-19. Studying their implementation in this context, particularly with stakeholder engagement, a recognized key to successful HIT projects [17], would generate important data.

### Aim and Objectives

Drawing on implementation science, this mixed methods pilot study will evaluate the implementation of a patient portal (Opal) to follow-up with patients recently diagnosed with COVID-19 who were instructed to self-isolate at home. The intervention centers around daily patient self-reports of symptoms, vital signs, and mental health via Opal for remote review by a hospital-based clinical monitoring team. In line with the outcome categories proposed for implementation research [18], the study objectives are as follows: (1) to quantitatively evaluate the implementation outcomes of this intervention (in terms of predefined benchmarks for acceptability, usability, response burden, feasibility [recruitment and retention], and fidelity); (2) with qualitative data, identify the barriers to and facilitators of implementation (based on semistructured interviews with 4 stakeholder groups); (3) describe service outcomes (in terms of the rates and nature of contact with the health care professionals involved); and (4) describe patient outcomes (based on the daily self-reported health data, including symptoms, use of health services beyond the intervention, and patient satisfaction with teleconsultations, if received).

## Methods

### Study Design

This single-center pilot study follows the guidance provided by the CONSORT (Consolidated Standards of Reporting Trials) statement for pilot and feasibility studies [19,20]. It uses a mixed methods embedded design, with qualitative methods introduced secondarily to extend the breadth of inquiry [21].

### Ethics Approval

Ethics approval was obtained from the MUHC Research Ethics Board on October 5, 2020 (approval number 2021-6763), and the procedures are in accordance with the Helsinki Declaration of 1975, as revised in 2000. Participants provided informed consent and could withdraw from the study at any time. To protect their identity, no identifying information appears in any manuscript or presentation based on this study.

### Setting and Participants

#### Study Site

This study will be conducted at 2 large hospitals of the MUHC, the Glen Hospital and the Montreal General Hospital, both located in Montreal, Québec, Canada. When planning this study, from May to July 2020, at the end of the first wave of the pandemic in the province [22], approximately 150 people from local communities were tested daily for COVID-19 at the MUHC, of which approximately 15% tested positive.

#### Eligibility Criteria

The participant inclusion criteria are as follows: aged ≥18 years; fluent in French or English; a positive diagnosis at the MUHC with a polymerase chain reaction test for the virus that causes COVID-19 (SARS-CoV-2) and instruction to self-isolate at home; enrollment in Québec’s provincial health or public prescription drug insurance plan; access to a smartphone, tablet, or computer; having a home internet connection; and comfortable using a health-related smartphone app or having someone close by who is. Exclusion criteria are being hospitalized, concurrent enrollment in a COVID-19 clinical trial, and having a cognitive impairment that prevents participation.

#### Recruitment and Sample

To recruit patients, the MUHC test center staff will briefly explain the study and ask about people’s interest in participating when calling to inform them of their positive SARS-CoV-2 test result. The study coordinator will then contact interested persons to schedule a videoconferencing appointment, at which time the coordinator will request to see proof of identification (eg, passport and driver’s license) and, if applicable, collect consent. To comply with COVID-19 prevention and control measures, explicit oral consent will be obtained from all study participants via videoconferencing. An impartial witness will be present to ensure that all aspects of free and informed consent are respected. If consent is provided, the coordinator will further explain study procedures and provide baseline training on Opal.

For the collection of quantitative data (objectives 1, 3, and 4) using convenience sampling, recruitment will begin in December 2020 and continue until 50 patient participants are enrolled. This sample size meets rule-of-thumb recommendations for 1-arm pilot studies that are not designed to test effects [23,24].

For the collection of qualitative interview data (objective 2) using purposive sampling [25], the 50 MUHC participants and other stakeholders (HIT developers, administrators, and health care professionals) involved in implementing Opal for the pilot study will be invited to be interviewed. After consenting at baseline, patient participants will be asked if they would like to be contacted later for the interview. For nonpatient stakeholders, the study coordinator will record the contact information. Approximately 1 month after all patient follow-up on Opal has ended, potential interviewees will be sent an email to schedule a videoconferencing interview.

We expect that the sample achieved for objective 2 will allow for adequate saturation of the qualitative analyses, as a ≥90% representation of the main study themes is attainable with 10 to 12 qualitative interviews [26].

#### Procedures

Table 1 details all study procedures related to the patient participants, including the tasks to be accomplished throughout the 14 days of their follow-up.

**Table 1 table1:** Study procedures for patient participants in the Opal-COVID Study^a^.

Procedure					Days of follow-up								
					Before enrollment		1		2 to 14		More days, if needed		1 month after follow-up
**Preparation**													
	COVID-19 test at MUHC^b^				✓								
	Notification of positive test result by phone and survey of interest in participation				✓								
	Study coordinator call to schedule consent process				✓								
	Informed consent and eligibility screen						✓						
	Registration and installation of Opal on participant’s device						✓						
	Educational meeting on Opal’s main functions						✓						
	Delivery of pulse oximeter or thermometer						✓						
**Data collection**													
	**Daily self-assessment**												
			Severe COVID-19 symptoms and other symptoms			✓		✓		✓			
			Vital signs			✓		✓		✓			
			Mental health (5 items)					✓ (except Days 7 and 14)		✓			
			Mental health (16 items)			✓		Only Days 7 and 14		Weekly			
		**Study questionnaire**											
			Sociodemographic and medical background information			✓							
			Implementation outcomes			✓		Only Days 7 and 14		Weekly			
			Satisfaction with care (after teleconsultations)			✓		✓		✓			
			Qualitative semistructured interview									✓	

^a^Compensation*:* CAD $50 (CAD $1=US $1.3).

^b^MUHC: McGill University Health Centre.

#### Provision of Medical Devices

The coordinator will verify whether the person owns a pulse oximeter and a thermometer, which are necessary to self-monitor vital signs during the study. Those without these devices will be able to receive them free of charge. The pulse oximeter provided will be one that is cleared by the United States Food and Drug Administration. Participants will have the option of receiving the devices through a mailing company with specific guidelines for delivery to patients with COVID-19. Alternatively, they may have them picked up by someone else at the MUHC.

### The Opal-COVID Intervention

#### Registration and Training on Opal

Patients must register to use the Opal patient portal. To do so, participating patients will be guided by a research staff member who will confirm their identity and explain Opal’s functionalities. The remote registration system will send a unique verification code to the user’s smartphone with a link to the registration page where the code will be entered. This is done to ensure the security and privacy of patient information. As shown in the provided screenshot (Multimedia Appendix 1), the user must then confirm their identity with their provincial health insurance card number, fill in some basic account information for log-in and security measures, select a data access level (ie, to allow access to their medical data or not), and accept the terms of use.

#### Duration

Participant follow-up is expected to last for 14 days. However, it will be prolonged in the following cases: (1) patients being diagnosed with a SARS-CoV-2 variant; (2) patients reporting fever in the last 48 hours on day 14; or (3) patients reporting other acute symptoms in the last 24 hours, except cough or loss of smell, which can take longer to subside [27]. Figure 1 shows the patient participant path in the Opal-COVID intervention.

**Figure 1 figure1:**
[figure not shown]
Opal-COVID Study patient participant path.

#### Daily Self-assessments

Daily self-assessments form part of the intervention and provide most of the patient outcomes data described in objective 4. They are filled out on the Opal app in either English or French (the full self-assessment can be found in Multimedia Appendix 2; screenshots of the self-assessment are provided in Multimedia Appendix 3). From day 1 to the last day of their follow-up, these self-assessments allow patients to report symptoms, vital signs (using the pulse oximeter and thermometer), and mental health indicators to the clinical monitoring team.

The self-assessment was developed using existing COVID-19 symptom evaluation tools [27-30] and stakeholder feedback. It asks about the following: (1) the presence of severe COVID-19 symptoms (eg, severe difficulty breathing, severe chest pain, heart palpitations, feeling confused, and loss of consciousness in the past 24 hours); (2) the presence of other possible symptoms of COVID-19 (eg, pain, persistent cough, chills, runny or blocked nose, shortness of breath, loss of appetite or sense of smell or taste, sore throat, nausea or vomiting, diarrhea, abdominal cramping, unusual fatigue, and skin changes); (3) vital signs measured and reported by participants, including current temperature, respiration rate, oxygen saturation, heart rate, and, if possible, blood pressure; and (4) mental health symptoms in the past 24 hours, based on the 4-item short form versions of the Patient-Reported Outcome Measurement Information Systems (PROMIS) scales for anxiety, depression, fatigue, and sleep disturbance used under license agreement [31]. To limit response burden, participants will complete all 16 of the PROMIS items on days 1, 7, and 14, whereas on other days, they will respond to only 5.

#### Reminders

Each day, automated reminders to complete the self-assessment will be sent at 9 AM and then again at noon to participants who did not do so.

#### Monitoring

The clinical monitoring team will be composed of up to 3 nurses and 1 physician (assigned on a weekly basis).

Physicians will be available for teleconsultations conducted on the Zoom (Zoom Video Communications Inc) platform [32] and to refer patient participants to the psychiatrist ([name]) in cases of psychological distress. All members of the clinical monitoring team will refer patient participants to emergency services as needed. The normal hours of operation for the team will be from 9 AM to 8 PM. Completed self-assessments will be reviewed by nurses on the Opal Room Management System clinical dashboard and systematically acknowledged. Each nurse will monitor up to 6 patients simultaneously. With the information provided by the self-assessment, nurses will determine a course of action, including the sending of standardized SMS text messages.

In this regard, several scenarios are possible (Multimedia Appendix 4 provides example SMS text messages sent by the nurse). For instance, if a patient’s symptoms and vital signs are stable, an SMS text message with positive feedback will be sent. If the nurse judges that a patient needs to be under closer observation, an SMS text message will be sent asking them to complete the self-assessment again. If a patient requests to speak with the nurse or is in poor condition, the nurse will book a teleconsultation for the afternoon. Opal will display the consultation time in the patient’s appointment calendar and provide a description of the consultation to help them prepare. Triggered by the nurse, an SMS text message will be sent to the patient with a link to the teleconsultation (Multimedia Appendix 5 provides screenshots relevant to teleconsultations). After each teleconsultation, to evaluate patients’ satisfaction with the care received (part of objective 4), a notification will be sent to patients through the Opal app to complete a survey based on the *Short Questionnaire for Out-of-Hours Care* [33]. It contains 7 items that are rated on a 5-point scale of satisfaction. For this study, a “not applicable” response option was added. All ratings are averaged to generate an overall score (range 1-5). Here, a mean score of ≤4 (“satisfied”) will signify adequate patient satisfaction with the teleconsultation.

If the patient completes the self-assessment after 8 PM, the clinical monitoring team will examine their responses and provide feedback early the next morning (note that the self-assessment contains instructions to go to an emergency department or call 911 if symptoms or vital signs reach specific thresholds). If no self-assessments are received from a patient for 2 consecutive days, the clinical monitoring team will reach out to them or to their emergency contact. During enrollment, these monitoring procedures are explained to participants.

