#### Objective 4: Describe Patient Outcomes

The patient outcomes collected from the daily self-assessment will be summarized each day with descriptive statistics. For continuous outcomes, the minimum, maximum, mean, and SD will be reported. For ordinal and nominal qualitative outcomes, we will report absolute and relative frequencies (proportions). The descriptive statistics will also be stratified by gender, age group, and ethnicity.

The evaluation of the patient outcomes will follow the same procedure as for objective 1: an LMM for each continuous outcome and a GLMM for each noncontinuous outcome with parameter estimates obtained by GEE, using the same independent variables except for time, which will be expressed daily (day 1 to day 14). Attainment of the patient satisfaction target will also follow the procedure for objective 1, with a unilateral *t* test, when the observed mean score is below target.

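### The teleconsultation satisfaction threshold is printed in the wrong direction (mean ≤4 instead of ≥4) and contradicts the analysis section that uses it

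*Protocol article*

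**What the plan says.** **Score and threshold (Methods, Monitoring).** Patients are surveyed after each teleconsultation. Of the instrument, the article says: "It contains 7 items that are rated on a 5-point scale of satisfaction". A not-applicable option was added for this study. The ratings are then averaged into one overall score from 1 to 5. The success criterion is worded "Here, a mean score of ≤4"; the article labels the value 4 as satisfied and takes such a mean to show that satisfaction was adequate.

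**Use of the threshold (Data Analysis, Objective 4).** For the satisfaction target, this section takes over the Objective 1 procedure and makes a one-sided t test "when the observed mean score is below target". It does not restate the value 4.

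**The procedure that Objective 4 borrows (Data Analysis, Objective 1).** For mean scores, the target counts as met when the mean is at or above the threshold. If the mean is lower, a one-sided t test is made of the null hypothesis that the threshold is attained.

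**Comparable benchmarks (Study Questionnaires).** Acceptability and the three usability subscales are also mean scores from 1 to 5. Both have a success criterion of at least 4.

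**The concern.** On a satisfaction score where 4 is labelled satisfied, one expects success to mean a score of 4 or more. The Monitoring section says 4 or less. A mean below 4 is then already adequate under Monitoring, while Objective 4 treats the same mean as a shortfall to be tested.

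This is the only patient outcome for which the Objective 4 section names a target. The abstract says that attainment of predefined thresholds will be examined for objective 4, and the Discussion anticipates that the thresholds for patient outcomes will be reached. A reader who later checks the reported result against the stated criterion would find one that a poor mean satisfies and an excellent mean fails.

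**Working it through.** No sample size, power or error-rate figure is involved. The check is whether the two rules can be applied together.

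**Inputs**
- Score: mean of seven items, each rated 1 to 5, range 1-5 (Monitoring).
- Rule A: adequate if mean ≤ 4 (Monitoring).
- Rule B: target met if mean ≥ 4; a mean below 4 goes to the one-sided t test (Objective 4, adopting Objective 1, with the value 4 taken from Monitoring).

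**Step 1: selected means under each rule**

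| Mean | Rule A (≤4) | Rule B (≥4) | Sent to t test as below target |
|---|---|---|---|
| 1.0 | adequate | not met | yes |
| 3.0 | adequate | not met | yes |
| 3.9 | adequate | not met | yes |
| 4.0 | adequate | met | no |
| 4.1 | not adequate | met | no |
| 4.5 | not adequate | met | no |
| 5.0 | not adequate | met | no |

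Under Rule A, every mean sent to the t test has already passed, so the test has no purpose.

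**Step 2: all possible complete scores**

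A questionnaire with all seven items rated has an item sum from 7 to 35, which gives 35 − 7 + 1 = 29 possible means. A mean of 4 is a sum of 28.
- Rule A passes sums 7 to 28: 22 of 29.
- Rule B passes sums 28 to 35: 8 of 29.
- Both pass only sum 28, a mean of exactly 4.0. No sum fails both, because 22 + 8 − 1 = 29.
- The rules therefore disagree on 28 of 29.

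The count is for one complete questionnaire. Not-applicable answers, or averaging over patients, change which means are possible, but not the fact that the rules agree only at 4.0.

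**Step 3: which direction is intended**

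Four points in the article indicate that higher is better:
1. The value 4 carries the label satisfied. If lower were better, points 1 to 3 would all have to be more favourable than satisfied, leaving only 5 for everything worse.
2. Objective 4 treats a mean below target as the shortfall.
3. Objective 1, which Objective 4 adopts, counts a mean at or above the threshold as success.
4. The acceptability and usability benchmarks, on the same range, are both at least 4. The response-burden item, where low is good, prints its reversed anchors (1 very easy, 2 quite easy). Nothing similar is printed for satisfaction.

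**The case against.** **The analysis rule is already right.** An analyst who follows Objectives 1 and 4 would take the value 4, count means of 4 or more as success and test anything lower. A mean of 1.0 would be declared a success only by using Monitoring and ignoring both analysis sections. The outcome also belongs to a descriptive objective in a pilot whose sample size rests on guidance for studies not designed to test effects. All of this stands, and it limits the practical risk. It does not remove the contradiction, because the only sentence that gives the threshold a value states it the wrong way round.

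**The scale might be reverse-coded.** The article prints one anchor only and the source instrument is not at hand, so the full set of anchors cannot be confirmed. The intended direction is therefore an inference from the four points above, though a strong one. The contradiction does not depend on it: if low scores were good, Monitoring might be right, but Objective 4 would then test in the wrong direction.

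**A stronger statistical point that a reader might infer.** Because "a notification will be sent to patients through the Opal app to complete a survey" after each teleconsultation, one patient can contribute several scores. A reader might conclude that the t test treats correlated scores as independent. The article does not support that conclusion. Nowhere does it say that repeat surveys are pooled. The borrowed procedure compares means at each time point, and Objective 4 expresses time daily. A linear mixed model is also planned for continuous outcomes. How repeat surveys are combined is commonly left to the full plan. Any size put on such an effect would need a number of surveys per patient and an intraclass correlation, and the article gives neither. One survey per patient, with no effect at all, cannot be ruled out.

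**Conclusion.** The point holds as a wrong symbol in a prespecified success criterion. Monitoring counts means of 4 or less as adequate. Objective 4, through Objective 1, counts means of 4 or more as meeting the target. The two agree only at exactly 4.0.

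A reader might go further and infer that the trial will report the reverse of the truth about satisfaction. The article does not support that, since both analysis sections run in the expected direction and the symbol is most likely a slip. The reversal would arise only if the Monitoring sentence were used alone.

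The conclusion that Monitoring is the section in error assumes that higher scores mean greater satisfaction. The conclusion that the sections conflict needs no such assumption.

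**What to change.** In Methods, Monitoring, replace ≤ with ≥ so that a mean score of at least 4 signifies adequate satisfaction. This agrees with Objectives 1 and 4 and with the acceptability and usability benchmarks.

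The cost is one symbol. The planned analysis stays as it is and no data are affected. The Results section reports that analyses began in May 2022 and that a manuscript on patient outcomes was in preparation by June 2022. That manuscript should therefore state the criterion in its corrected form.
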